#### Sensorimotor performance

To measure lower extremity function we will use the Short Physical Performance Battery (SPPB) [65] comprising measures of balance, walking speed, and sit-to-stand ability. Individual subtest scores range from 0 to 4, resulting in a summary score ranging from 0 to 12. Lower SPPB scores represent reduced physical abilities and have been associated with greater frailty [66] though previous studies demonstrated that physical activity interventions can result in improved SPPB scores [67].

We will use a modified version of the Clinical Test of Sensory Integration of Balance (CTSIB) [68] to estimate how well subjects can utilize vision, somatosensation, and vestibular information for the maintenance of postural stability. Subjects are required to maintain their feet side-by-side for 30 s with eyes open on a firm surface, eyes closed on a firm surface, eyes open on an unstable surface, and eyes closed on an unstable surface.

Upper extremity function will be assessed using the Purdue Pegboard Test (PPT) [69] requiring participants to place cylindrical metal pegs into holes either with the dominant, non-dominant or both hands simultaneously within a given time. In a fourth condition, participants have to combine pegs, washers and small tubes into a pre-defined assembly. Thus, the test measures fine and gross motor dexterity as well as coordination of hands, fingers, and arms [70] and poor PPT performance has been shown to be associated with age-related frailty [71].

#### Sensory functioning

In the sensory domain, we will assess visual, tactile, and auditory functioning. Visual testing will be carried out using the automated Freiburg Vision Test (FrACT) [72, 73]. For visual acuity testing, we will use Landolt Cs and Snellen Es of different size and orientation depicted on a computer screen in a pre-defined distance and under standardized lighting conditions. Visual contrast sensitivity will be assessed using Landolt Cs and gratings of different orientation and level of contrast.

Tactile discrimination performance will be tested in the form of a grating orientation task using hemispherical plastic domes (JVP Domes, Stoelting Europe, Dublin, Ireland), which have parallel bars and grooves of equal width on their surface (15 domes with a width range of 0.35 to 12 mm). To determine grating orientation thresholds, gratings are manually applied by the experimenter to the subjects’ skin (right index finger pad, right ring finger pad, right lower lip, in a randomized order) and subjects are to indicate the orientation of the grating (vertical, horizontal).

Fine-touch thresholds will be evaluated by probing the fingertips of the dominant second and fourth digit as well as the back of the dominant hand using von Frey filaments (Marstocknervtest, Marburg, Germany). Touch forces range from 0.25 mN to 512 mN on a logarithmic scale. Thresholds will be determined by using a staircase procedure [74].

To assess auditory acuity, hearing thresholds within the frequency range from 0.125 to 8 kHz will be determined in the form of an audiogram using a screening audiometer (MA 25, MAICO Diagnostics GmbH, Berlin, Germany). Based on a staircase procedure, single tones will be presented via headphones separately to the right and left ear in a counterbalanced sequence.

#### Cognitive testing

Previous research demonstrated that physical frailty might be associated with changes and impairments in a number of cognitive domains, such as episodic, semantic, and working memory [75], perceptual and psychomotor speed [75, 76], executive function [77] and top-down attention [78]. To assess cognitive abilities we will select four subtests of the *Cambridge Neuropsychological Test Automated Battery* (CANTAB; Cambridge Cognition (2019), www.cantab.com).

The *Reaction Time (RTI)* test assesses information processing speed, allowing for separate estimates of mental and motor response speed.

Using the *Attention Switching Task (AST)* we will examine top-down attentional control defined as the ability to flexibly switch attentional resources towards relevant information and inhibit irrelevant information. Dependent measures include response time and accuracy, switching cost and congruency cost.

Using the *Spatial Span (SSP)* test, we will assess working memory span to obtain an estimate of visuospatial working memory capacity.

Finally, we will investigate the integrity of fronto-striatal pathways using the *Intra-Extra Dimensional Set Shift (IED)*, which is a computerized version of the Wisconsin Card Sorting test. The IED is a test of executive functioning including rule acquisition and reversal as well as attentional set formation maintenance, shifting and flexibility of attention.

#### Functional level and quality of life

To assess function in frail elderly at a very low activity level, we will apply the Frail Elderly Functional Assessment (FEFA) [79], which has been demonstrated to be valid, reliable, and sensitive to change [80]. Using the German version of the Center for Epidemiologic Studies Depression Scale (CES-D), we will assess depressive symptoms experienced in the past week based on a 20-item self-report scale [81, 82]. Overall health status and quality of life will be evaluated using the Short Form-36 Health Survey (SF-36) [83] and the EuroQol-5D-5L (EQ-5D-5L) [84]. The SF-36 is a widely used survey of quality of life in health economics and allows for evaluation of patient health on physical and mental health scales. The EQ-5D-5L quantifies health status in five dimensions and on a visual analogue scale ranging from 0 to 100. To estimate functional capacity of the participants, we will use the self-report version of the Marburg Competency Scale (Marburger Kompetenz Skala, MKS) [85], which involves 30 questions on competence in typical everyday activities. Falls self-efficacy will be measured using the Falls Efficacy Scale – International Version (FES-I) [86], a self-report questionnaire assessing the level of concern regarding the possibility of falling when performing certain activities of daily living. To screen for malnutrition, we will use the Mini Nutritional Assessment (MNA) [87].

#### BDNF serum level assessment and genotyping

Blood samples collected by the study psychiatrist will be processed according to standard protocols and stored at − 80 °C until analysis. BDNF serum levels as a marker of synaptic plasticity will be measured using a highly sensitive fluorometric enzyme-linked immunoabsorbent assay (ELISA). For genetic analyses, we will extract DNA from blood samples. GWAS analysis will be performed on an Illumina GSA1.0 SharedCustom Content bead array according to the manufacturer’s instructions. GenomeStudio 2.0 software will be used to determine BDNF genotypes and results will be exported in PLINK format.

### Data analysis and handling

We will use mixed repeated measures analyses of variance for each of the outcome variables in order to assess the effect of the training at baseline, after 60 days, and after 90 days, as well as to unveil differences between the two groups. Significant time-by-group interactions will be further examined using post-hoc tests. To evaluate changes through the interventions, pre-post effect sizes will be computed and compared across interventions. The problem of missing data will be handled using multiple imputation.

Data collected in this project will be recorded, stored and analyzed anonymously. A list assigning codes to names will be stored separately under high security standards. Analysis of the data will be of scientific purpose only.

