We hypothesize that the sensorimotor training will have superior effects on frailty status compared with the control training, as reflected by a pre-to-post reduction in frailty indices and an improvement in frailty-related everyday functioning. On the neuronal level, we expect a refinement of sensorimotor representation maps and an increase in neuronal efficiency in the brain. Furthermore, we expect that such neuroplastic changes will be mirrored by a pre-to-post increase in BDNF serum levels. In addition, we will compare frailty-associated outcomes between BDNF genotypes that were shown to differ in terms of both BDNF secretion and the magnitude of training-related improvement [27, 38]. In the sensorimotor domain, we expect an increase in movement speed as well as an improvement in lower extremity motor function such as balance, and upper extremity motor function such as dexterity. With regard to sensory abilities, we expect an increase in visual, tactile, and auditory performance scores. Lastly, we expect the sensorimotor training approach to enhance psychological wellbeing, as reflected by an increased perceived health status and quality of life.

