**Fig. 1 Fig1:**
[figure not shown]
Expected flow of participants and study design

The inclusion criteria will be an age of 65 to 95 years and the presence of at least one of the five frailty phenotype criteria [39], i.e. self-reported unintentional weight loss of > 5 kg in the prior year, self-reported exhaustion, low level of physical activity specified in kcal/week, muscle weakness as measured by low grip strength using a Jamar hand dynamometer, and slowness by slowed gait speed over 4.57 m. According to the phenotype model, the presence of one or two criteria is considered as pre-frailty while the presence of three or more criteria is considered as frailty [39]. We will include pre-frail as well as frail persons to investigate neuroplasticity mechanisms across a broader range of age-related functional decline, as the pre-frail stage is considered to describe a condition at high risk of progression to frailty [40, 41] and may be more amenable to change. Exclusion criteria will be: acute bone fractures within the last 3 months, immobility, paralysis or confinement to bed; stroke or neurological disorders with major cognitive or physical impairments; dementia; myocardial infarction within the last 6 months; life-time prevalence of mental disorders such as schizophrenia and other psychotic disorders, bipolar disorder, obsessive-compulsive disorder, post-traumatic stress disorder, drug or alcohol addiction; current severe major depression or other acute axis 1 mental disorders; current intake of benzodiazepines or antipsychotics; vitamin B12-, folate- or thyroid-stimulating hormone deficiency. Specific exclusion criteria will be examined during the first visit and include: cognitive impairment defined as a Mini Mental State Examination (MMSE) score of ≤ 24; severe impairments in sensory abilities (i.e. visual acuity of < 0.1; mechanical detection threshold of > 512 mN; severe or profound hearing loss according to the WHO, defined as a mean hearing threshold of > 60 dB; severe tinnitus symptomatology).

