### Sample size

Previous studies in healthy older humans using sensory training have achieved promising results with medium effect sizes and sample sizes of 41 to 53 subjects [5, 32]. Given that our training includes a multimodal stimulation approach and focuses on motivational enhancement within a virtual training environment, we assume that in our participants the effect of the experimental training program would exceed a medium effect size. To estimate sample size, we use a repeated measures design with one between-factor with two groups and one within-factor with three assessment points [43]. Assuming a medium effect size of Cohen’s f = 0.25, 95% statistical power, a correlation of 0.50 between the dependent measurements, and a two-sided alpha error level of .05, we therefore would need 22 participants in each group. To account for a drop-out rate of about 25% during the training, we will include 30 subjects per group (60 in total).

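### The primary comparison is an omnibus group-by-time test over baseline, day 60 and day 90, which does not isolate the end-of-training difference that the hypothesis concerns

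*Protocol article*

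**What the plan says.** The hypothesis, under Objectives of the study in the protocol article, is directional and comparative: "We hypothesize that the sensorimotor training will have superior effects on frailty status compared with the control training", shown by a reduction from before to after training. The Abstract and Design sections put the end of training at day 90 (assessment 2).

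The Data analysis and handling section states the method: "We will use mixed repeated measures analyses of variance for each of the outcome variables". All three assessments (baseline, day 60 and day 90) enter this model. The section continues: "Significant time-by-group interactions will be further examined using post-hoc tests". It adds that "pre-post effect sizes will be computed and compared across interventions" and "The problem of missing data will be handled using multiple imputation".

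The Sample size section uses the same structure: "one between-factor with two groups and one within-factor with three assessment points", with f = 0.25, power 95%, correlation 0.50 and two-sided alpha .05. This gives 22 per group, raised to 30 for about 25% drop-out.

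The primary outcome is the frailty phenotype. Table 1 schedules it at all three assessments and lists it as a status (pre-frail, frail).

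**The concern.** With two arms and three assessments, the group-by-time interaction has 2 degrees of freedom. It rejects for any departure from parallel mean curves, in either direction and at any assessment. The hypothesis concerns one comparison: sensorimotor against relaxation at the end of training, given where participants started.

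Two things are at stake. First, a significant primary test may come from day 60 alone, before the third 30-day phase (the sensorimotor tasks) has been delivered. Second, if the benefit grows or holds up to day 90, part of the test is spent on a comparison the hypothesis does not need, and baseline enters as one of the repeated outcomes rather than as a covariate. The post-hoc tests are conditional on the omnibus result and no contrast is fixed, so the article does not settle which estimate will answer the trial's question.

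**Working it through.** **Inputs.** From the Sample size section: two groups, three assessments, correlation ρ = 0.50, f = 0.25, two-sided alpha .05, 22 per group (N = 44), 30 per group after drop-out. Assumed here: between-arm differences of 0.5 and 0.8 SD, the time courses, a continuous outcome, and equal correlation between all pairs of assessments.

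**Step 1: reproduce the protocol's figure.** For the interaction, λ = f² × N × 3 / (1 − ρ) = 0.0625 × 44 × 3 / 0.5 = 16.5, with 2 and (44 − 2) × 2 = 84 degrees of freedom. Power is 0.956. With N = 42 it is 0.946, so 44 is the smallest even total and 22 per group is confirmed. A between-group main effect would need N = 142. The trial is therefore sized on the 2-df interaction. Drop-out: 22 / 0.75 = 29.3, rounded up to 30.

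**Step 2: the two tests for a given pattern.** Let d₀, d₆₀ and d₉₀ be the between-arm differences in SD, with d₀ = 0 by randomisation, and n the number per arm.

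- Omnibus: λ = (n/2) × S / (1 − ρ), where S is the sum of squared deviations of the three differences from their mean.
- Baseline-adjusted day-90 contrast: noncentrality d₉₀ / √[(1 − ρ²) × 2/n], on N − 3 = 41 degrees of freedom. With n = 22 the denominator is √(0.75 × 2/22) = 0.261.

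Worked example, 0.8 SD linear in days: the differences are 0, 0.533 and 0.8, with mean 0.444, so S = 0.1975 + 0.0079 + 0.1264 = 0.332. Then λ = 11 × 0.332 / 0.5 = 7.30 and omnibus power is 0.66. The contrast has noncentrality 0.8 / 0.261 = 3.06 and power 0.85.

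**Step 3: results at 22 per arm, ρ = 0.50.**

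| Pattern (d₆₀, d₉₀) | Omnibus | Adjusted day-90 contrast |
|---|---|---|
| 0.8 SD, linear (0.53, 0.8) | 0.66 | 0.85 |
| 0.8 SD, plateau (0.8, 0.8) | 0.77 | 0.85 |
| 0.5 SD, linear (0.33, 0.5) | 0.30 | 0.46 |
| Day 60 only (0.8, 0) | 0.77 | 0.05 |
| Fading (0.8, 0.6) | 0.68 | 0.61 |
| Fading (0.8, 0.5) | 0.65 | 0.46 |

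With 30 per arm the first row becomes 0.80 against 0.94, the third 0.40 against 0.59, and the day-60-only row 0.90 against 0.05. For 0.8 SD linear at 22 per arm, the contrast also leads at ρ = 0.3 (0.51 against 0.78) and ρ = 0.7 (0.88 against 0.95).

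**Step 4: the protocol's own effect size.** For this interaction f² = S/12, so f = 0.25 means S = 0.75. A plateau or a day-90-only effect then has d₉₀ = √(0.75 × 3/2) = 1.06 SD, and equal steps have d₉₀ = √(0.75 × 2) = 1.22 SD. The omnibus test has 0.956 in each case; the adjusted contrast has 0.978 and 0.996. The gain is 2 to 4 points.

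**Step 5: simulation** (20,000 trials per pattern, N = 44). Under no effect the rejection rates are 4.9% (omnibus) and 5.2% (contrast). For a day-60-only difference of 1.06 SD they are 95.7% and 5.1%.

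**The case against.** The other side has several good points.

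- **Sizing and analysis agree**, and the interaction test holds its type I error. A reader might infer that the test is invalid or the trial wrongly sized; Steps 1 and 5 show neither.
- **The power loss is conditional.** It depends on the time course and is small at f = 0.25. If a real effect peaks at day 60 and partly fades, the omnibus test is the stronger one. A reader might infer that the change costs nothing; that does not hold.
- **Post-hoc tests can show where and in which direction the arms differ**, and the article does not declare a significant interaction to be success at day 90. This softens the day-60 problem. It does not remove it, because no contrast is named and the tests run only after omnibus significance.
- **Regression to the mean.** Entry requires "the presence of at least one of the five frailty phenotype criteria", and the same phenotype is the primary outcome, so a reader might infer that the pre-post effect sizes will overstate benefit. The documents do not support that as a flaw in the comparison: the effect sizes are to be compared across randomised arms with the same entry criteria, so regression to the mean cancels in expectation.
- **An unseen analysis plan may name covariates and contrasts.** True, and their absence alone would be no finding. But the article itself states the test, and the sample size rests on it.
- **The primary outcome is listed as a category**, so the percentages are indicative and do not transfer directly to it.

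**Conclusion.** The concern holds in a limited form. The planned test is valid but answers whether the two curves differ anywhere, not whether the arms differ at the end of training. A day-60-only difference of 0.8 SD would make it significant in about 77% of trials. For effects that grow or hold to day 90, it gives up 8 to 19 points of power at 0.8 SD (plateau and linear) and about 17 points at 0.5 SD (linear), but only 2 to 4 points at f = 0.25. These figures rest on the protocol's correlation of 0.50, 22 per arm, assumed effects and time courses, and a continuous outcome. The change should be made; it does not put the trial's validity in question.

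**What to change.** Name one primary estimate: the day-90 between-arm difference with its 95% CI, from a model with assessments 1 and 2 as outcomes and the baseline value as covariate. Use an ordinal or binary equivalent if the phenotype is analysed as a count or a category. Keep the day-60 difference and the overall interaction as secondary. Report the adjusted difference alongside the compared pre-post effect sizes. Multiple imputation can stay, applied consistently with this model.

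The cost is wording: the primary outcome is already scheduled at all three assessments. The statistical cost is lower power if the effect peaks at day 60 and fades, for example 0.61 instead of 0.68 when 0.8 SD falls to 0.6 SD. The secondary day-60 analysis would still show such a pattern.

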### Ethics and dissemination

The study has been approved by the local Ethics Committee (Medical Ethics Committee II, Medical Faculty Mannheim, Heidelberg University; 2015-544 N-MA) according to the Declaration of Helsinki and has been registered under the trial number NCT03666039. If any important changes apply to the trial protocol, the trial registration will be updated. Any personal information of study participants will be stored and protected in accordance with the most recent General Data Protection Regulation of the European Union and will be monitored by the department’s data protection commissioner. Direct access to data will be restricted to authorized representatives from the host institution and the regulatory authorities. The results of the study will be submitted for publication in a selected peer-reviewed journal on geriatrics and presented at relevant international conferences.

Participants will be informed about all procedures and written informed consent will be obtained. Any severe adverse events caused by our assessments or treatment protocols will be recorded and analyzed. During assessments, participants will be monitored by the investigator at all times and on a regular basis during the training procedures to maintain the opportunity to intervene if any unintended effects occur. A physician is available in cases of emergency. During measurements, the institute’s liability insurance protects the participants against mishandling of the investigator.

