## Methods

### Design

This randomized controlled trial will compare a tablet-based sensorimotor training (experimental group) and a tablet-based relaxation training (control group) in subjects suffering from frailty. Both conditions are conceptualized as a 90-day home-based intervention. Assessments will take place (1) before (baseline), (2) after 60 days (assessment 1) and (3) at the end of training (90 days; assessment 2) at the Institute of Cognitive and Clinical Neuroscience, Central Institute of Mental Health, Mannheim.

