### Randomization and blinding

Subjects will be randomly allocated on a 1:1 ratio to either the experimental or control condition. The randomization schedule will be generated electronically by a researcher not involved in the assessments. Group allocations will be kept in sequentially numbered sealed opaque envelopes. Participants will be informed about the random allocation procedure. Blinding of the investigator will not be possible because the investigator will conduct parts of the assessments and training procedures.

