### Interventions

#### Experimental condition

The interactive tablet-based sensorimotor intervention will consist of three consecutive training phases with each phase comprising 30 days (90 days in total). The first phase will consist of unimodal sensory discrimination tasks in the visual, auditory and tactile domain to increase distinctiveness and acuity of cortical sensory representations. In the second phase, subjects will be trained on bimodal sensory integration using visual-auditory, visual-tactile and auditory-tactile tasks. Bimodal sensory integration will require subjects to process stimuli of two different perceptual modalities and judge whether the two stimuli are synchronous or not. These tasks are assumed to increase temporal acuity for multisensory integration and to promote plasticity in perceptual integration brain networks [44, 45]. Unimodal and bimodal stimuli are presented through the tablet involving explicit answers on the tablet’s touch screen. The third phase will require participants to process bimodal sensory information in order to control a sensorimotor response, in the form of visual-auditory guided cycling, visual-tactile determined grasping, and auditory-visual controlled hands coordination. In these sensorimotor integration tasks, sensory input must be interpreted and integrated in terms of the current state of the motor system to continuously adjust motor commands and behavior [46]. These tasks aim at improving motor acuity, i.e. to increase precision and reduce variability of motor performance by increasing the signal-to-noise ratio in sensorimotor brain networks [47, 48]. For tactile, cycling, and grasping tasks, we will use external devices that are wirelessly connected to and controlled by the tablet (i.e. a Braille display device for tactile tasks, a customized ergometer for cycling tasks, and a handgrip dynamometer for grasping tasks).

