### Strengths and limitations

The present study has several strengths. First, the study includes an innovative multimodal sensorimotor approach designed to specifically target mechanisms of pathological neuroplasticity in frailty, compared to an active control condition. Second, participants will be recruited from the general population instead of clinical institutions. This will increase generalizability of the results and approach. Third, the treatment procedures are conceptualized as home-based training, thereby presumably increasing compliance for daily care.

The study is also subject to some limitations. Researchers and participants will not be blinded to treatment condition. However, by randomly assigning subjects to the treatment conditions and by using an appropriate active control group, we aim to eliminate any effects of expectations or systematic biases from inducing performance differences. The study design does not include follow-up assessments going beyond post-training measurements after completion of the training, which should be addressed in future studies.

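### The article's one adverse-event rule makes severity and causation by the study conditions of recording, so in this unblinded trial the recorded counts would not give an unbiased comparison of harm between arms

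*Protocol article*

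**What the plan says.** The protocol article, under Ethics and dissemination, commits to this: "Any severe adverse events caused by our assessments or treatment protocols will be recorded and analyzed". The following sentence provides for watching participants throughout assessments and "on a regular basis during the training procedures to maintain the opportunity to intervene if any unintended effects occur". That describes a readiness to act. It does not say that what is seen is written down.

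On blinding, Randomization and blinding states: "Blinding of the investigator will not be possible because the investigator will conduct parts of the assessments and training procedures". Strengths and limitations adds: "Researchers and participants will not be blinded to treatment condition".

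On population and setting, the article says "The inclusion criteria will be an age of 65 to 95 years and the presence of at least one of the five frailty phenotype criteria", and under Design "Both conditions are conceptualized as a 90-day home-based intervention". The experimental arm's external equipment includes "a customized ergometer for cycling tasks, and a handgrip dynamometer for grasping tasks"; cycling and grasping belong to the third 30-day phase. The control arm watches nature videos or follows guided relaxation.

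Table 1 lists no count of falls, injuries or admissions. The FES-I is there, but it measures concern about falling, not falls. Clinical history and medication are self-reported at T0, T1 and T2.

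**The concern.** A randomised trial learns what its intervention causes by comparing all events between arms. If causation is a condition of entry to the record, the question is answered event by event before the comparison is made. The background events of the control arm, which are the comparator, are then among those that need not be recorded. A protective effect is also hard to see: if training prevented falls, the falls that remained would mostly not be caused by the study and so would not have to be counted.

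This matters more here than in many trials. Participants are pre-frail or frail, aged 65 to 95, and train at home for 90 days. The article's own Background links inactivity to falls and fractures. Allocation is open, and one arm contains physical tasks that the other does not.

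**Working it through.** **What the rule lets through.** Two conditions, both from the sentence under Ethics and dissemination:

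| Event | Severe? | Attributed to the study? | Recording required? |
|---|---|---|---|
| Severe fall during home cycling, attributed to it | yes | yes | yes |
| Minor fall or pain after a session | no | yes | no |
| Hospital admission thought unrelated, either arm | yes | no | no |
| Non-severe fall on a day without training, either arm | no | no | no |

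Only the first row is covered.

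**Whether anything else in the article fills the gap.**
- Monitoring during training (Ethics and dissemination): aimed at intervening; recording is not mentioned.
- Clinical history at T0, T1 and T2 (Table 1): the same in both arms, but not described as collecting harms.
- Physical examination (Procedure): repeated after 60 days. With three phases of 30 days, the cycling and grasping phase starts after day 2 × 30 = 60, so that examination comes before it.
- Frailty index at all three visits: a score over 40 deficits, which could shift with new disease but does not list events.

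None of these is a second recording rule.

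**How the rule can distort a comparison.** The number per arm comes from Sample size: 22 / (1 − 0.25) = 29.3, rounded up to 30, which agrees with the plan. Let p be the true 90-day risk in an arm and c the share of events that pass both conditions. Then:

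- expected recorded events = 30 × p × c
- recorded risk ratio = true risk ratio × (c in training arm / c in control arm)

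The article gives neither p nor c. The values below are assumptions chosen to show the mechanism.

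*Equal true risk, unequal attribution (c = 0.50 training, 0.10 control):*

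| True risk, both arms | True events per arm | Recorded, training | Recorded, control | Recorded ratio |
|---|---|---|---|---|
| 10% | 3 | 1.5 | 0.3 | 5 |
| 20% | 6 | 3.0 | 0.6 | 5 |
| 30% | 9 | 4.5 | 0.9 | 5 |

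With c = 0.30 and 0.05 the ratio is 0.30 / 0.05 = 6.

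*Opposite direction.* Suppose true risks are 30% (training) and 10% (control), with c = 0.10 and 0.30. Recorded events are 30 × 0.30 × 0.10 = 0.9 and 30 × 0.10 × 0.30 = 0.9. A true ratio of 3 appears as 1. The direction depends on who attributes what, and the article does not settle that.

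*Equal attribution in both arms.* The ratio is then unbiased, but information is lost. For true risks of 10% and 30%, 30 per arm, two-sided 5%, normal approximation:

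| Share recorded | Expected events | Power |
|---|---|---|
| all | 3 and 9 | 0.49 |
| 50% | 1.5 and 4.5 | 0.25 |
| 25% | 0.75 and 2.25 | 0.14 |
| 10% | 0.3 and 0.9 | 0.08 |

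The approximation is rough at such small counts; only the ordering should be relied on.

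**What a clean record would mean.** Zero events among 30 gives an upper 95% bound of about 3/30 = 10% for the kind of event that was recorded. For harm in general, the bound holds only if every event is captured.

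**The case against.** The strongest reply is that the sentence promises something about one class of events and excludes nothing. It stands in a short ethics paragraph of a journal article, and definitions, forms and attribution procedures normally sit in the full protocol. This is partly right. Missing procedural detail would be no finding. But the article does not stay silent: it states a rule, and that rule, followed as written, does not require the other events to be recorded.

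A reader might infer more than the text supports:

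- *That other events will never be recorded or will be missed.* The article does not say so. Some may surface in the self-reported clinical history, and a severe fall attributed to training is covered.
- *That the unblinded investigator judges causation.* No section names who does. The blinding sections make it plausible, no more.
- *That attribution will fall almost entirely on the training arm.* The rule also covers harm from assessments, which both arms undergo, and cycling and grasping occupy only the last third of training. A difference by arm is possible, but its direction and size are not fixed.
- *That the rule undermines the handling of missing data.* Data analysis and handling names multiple imputation and does not tie it to reasons for drop-out.

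It is also true that the objectives contain no safety hypothesis, and that 30 per arm gives an imprecise safety comparison even with full recording. That limits what the data could show. It is no reason to filter them at entry.

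**Conclusion.** The point holds in a limited form. The article's only recording rule for adverse events requires severity and causation together, so non-severe or unattributed events need not be recorded in either arm. Because allocation is open and the arms differ physically, the share passing the rule can differ by arm, and counts collected under it would not give an unbiased comparison of harm.

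The size is not estimable from the document. The apparent ratios of 5 and 6, and the masking of a true ratio of 3, rest wholly on assumed risks and attribution shares. The conclusion itself needs only two premises, the wording of the rule and the absence of blinding, and the article states both. It assumes that no fuller document widens the rule; if one does, the article's sentence should be brought into line with it. The efficacy analysis and the sample size are not affected.

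**What to change.** Replace the sentence under Ethics and dissemination with a rule along these lines: all adverse events, including falls and hospital admissions, are recorded in both arms from the first training session to T2, whatever their severity or presumed cause. They are elicited by the same standard question in both arms at T1, T2 and the existing training contacts. Severity, seriousness and relatedness are classified afterwards, and the number of events and of participants with events is tabulated by arm. Classification by someone unaware of the arm would be preferable where feasible.

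The cost is one sentence, a short question at visits and contacts already planned, and a little more data entry. No extra visits or staff are needed. The tabulation should be presented as descriptive, given 30 per arm.
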